### Interventions

All interventions will be administered and monitored via the online interface. Both the BA and physical exercise groups will receive therapist support, provided by the above-mentioned clinical psychology master’s students, supervised by an experienced clinical psychologist.

#### Physical exercise

Based on the screening data, an individualised exercise program, specifying intensity, frequency and duration of physical activity, will be provided for each participant in treatment groups 1 and 2, just prior to the treatment period commencing. A user-friendly pulse-watch, and/or pedometer will also be provided. Participants register their physical activity and receive automated, individualised feedback. The physical exercise intervention will run for 12 weeks, divided into 12 weekly modules.

#### Behavioural activation (BA)

The BA intervention provided to groups 3 and 4 will feature a variety of behaviour change strategies, including mapping of current behaviour, finding reinforcing activities and creating a difficulty-ranked hierarchy of these activities, activity scheduling and structuring, self-monitoring of mood and activity, and so on. Each participant will receive approximately 15 min of therapist support per week. The BA intervention will run for 12 weeks, divided into 12 weekly modules.

#### BA treatment rationale

The treatment rationale provided to treatment group 3 will be similar to that used in a popular self-help book [29] for treatment of depression. According to this rationale, individuals suffering from depression are trapped in a Trigger-Response-Avoidance-Pattern: a vicious circle of avoidance leading to less and less reinforcing stimuli. In accordance with this, BA serves to break the vicious circle and thereby relieve the individual of depressive suffering. Treatment group 4, which will not be provided with the TRAP rationale, will instead be informed that previous research indicates that activation improves wellbeing. Group 4 will receive the same amount of therapist support as group 3.

#### Physical exercise treatment rationale

Both groups 1 and 2 will be informed that physical exercise has been shown to decrease depression and especially fatigue, one of the core symptoms of depression. In addition to this, group 2 will also be provided with a fuller treatment rationale, according to which depression should be seen in the context of a vicious circle of lessened activity and energy levels. Both groups will receive the same amount of therapist support.

#### Control group

The waiting list control group will perform weekly measurements and receive automated, individualised feedback in graphic and message form comparing the recent results with those from previous weeks. After a 12-week delay, the group members will be randomised to one of the four treatment groups and receive treatment accordingly.

#### Relapse prevention

After the 12 treatment weeks and immediate post-treatment measurements, 50% of each treatment group of each recruitment cycle will be offered a relapse prevention program. The program will be based on and be similar to that used in a previous study [30] on relapse prevention for people suffering residual depressive symptoms after having previously received either psychotherapy or anti-depressant medication. The Internet-administered, therapist-assisted, progressive module-based program featured many of the standard components of cognitive behavioural therapy, including psychoeducation, BA, goal formation and mindfulness exercises.

### Instruments

All questionnaires will be administered via the Internet except for the clinical interviews, which will be conducted via telephone. Both these administration formats are considered valid methods of acquiring data [28,31].

#### Demographic and attitude data

At screening, data on sex, age, marital status, educational level, and so on will be collected to allow analysis of factors influencing treatment outcome and willingness to seek treatment. For the same purpose, ratings of the participants’ views on treatment credibility and expected results will also be recorded at screening using the five-item Treatment Credibility Scale (TCS) [32]. Participants will be administered the TCS for both the BA intervention and the physical exercise intervention, separately, after having read a brief description of the two interventions. Based on the parity of their participant ID number, the participants will then be randomised to either answer the TCS about BA first and then the same five questions about physical exercise, or *vice versa*. Participants will also answer what intervention they would prefer and to what degree.

#### Diagnosis

Initial diagnosis of depression, according to DSM-IV criteria, will be made using part A of the structured Mini-International Neuropsychiatric Interview (MINI) [27]. Additionally, each follow-up month, 33% of each treatment group will be interviewed per telephone. Hence, on an individual level, interviews will be conducted every third month during the follow-up period of 24 months (namely, eight follow-up interviews in total for each participant). On a group level, interviews will be conducted every month. The built-in data-loss of 66% each month will however be data missing completely at random since the participants are randomised to their respective months, making the procedure unbiased (see [33]).

#### Primary outcome

PHQ-9 [20] is the depression module of the Patient Health Questionnaire (PHQ), designed to score each of the nine DSM-IV criteria for depression as ‘0 (not at all)’ to ‘3 (nearly every day)’, allowing it to be used as both a diagnostic instrument and symptom severity scale. PHQ-9 has been shown to have good internal consistency (Cronbach’s alpha 0.86 to 0.89), good diagnostic validity [34,35] and adequate sensitivity to be used as an outcome measure [36,37]. Participants will complete the PHQ-9 weekly during the treatment period, immediately upon completion of treatment and then monthly during follow-up (24 months).

#### Secondary outcomes

In addition, three secondary outcome measures will be used. The International Physical Activity Questionnaire (IPAQ) [21] was designed to be a cross-nationally valid self-reported measure of physical activity, and features questions on the amount of time (minutes, hours and days) spent in the last 7 days on physical activity and sitting still. IPAQ will be administered upon treatment completion and thereafter at the 12- and 24-month follow-ups.

The seven-item general anxiety scale, GAD-7 is used for assessing anxiety and screening for generalised anxiety disorder, with psychometric evaluation having yielded good internal consistency (Cronbach’s alpha 0.92) and a good factorial structure (69% to 81% of variance explained) [23]. GAD-7 will be administered upon treatment completion and thereafter monthly during the follow-up period.

The Quality Of Life Inventory (QOLI) [22] will also be included. QOLI features 32 items ranging over 16 areas of life (health, economy, work, and so on) and has good internal consistency (Cronbach’s alpha 0.77 to 0.89) and test-retest reliability (0.80 to 0.91) [22]. QOLI will be administered upon treatment completion and thereafter at the 12- and 24-month follow-ups.

At screening, as well as immediate after treatment and at the 12- and 24-month follow-ups, participants will also answer the EQ-5D [38] to assess generic health status, and the Trimbos/iMTA questionnaire for Costs associated with Psychiatric illness (TiC-P) [39] to assess health economic aspects.

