**Methods/Design:**

This randomised controlled trial will include 500 participants meeting the diagnostic criteria for major depression, recruited in multiple cycles and randomised to either a waiting list control group with delayed treatment, or one of the four treatment groups: (1) physical exercise without a clear treatment rationale; (2) physical exercise with treatment rationale; (3) behavioural activation with treatment rationale; or (4) behavioural activation without a clear treatment rationale. Post treatment, half of the participants will be offered a relapse prevention program. Primary outcome measure will be the Patient Health Questionnaire 9-item. Secondary measures include diagnostic criteria for depression, as well as self-reported anxiety, physical activity and quality of life. Measurements - done via telephone and the Internet - will be collected pre-treatment, weekly during treatment period, immediately post treatment and then monthly during a 24-month follow-up period.

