Initial selection of participants will be based on the results of the online screening instruments, consisting of MADRS-S, PHQ-9 [20], IPAQ [21], QOLI [22], GAD-7 [23] (see below) and a number of additional questions on demographics and previous treatment experiences. While the other instruments return as outcome measures (see below), MADRS-S will only be used in the screening procedure as a measure of the severity of depression symptoms. Previous research has shown that MADRS-S has a good internal consistency (Cronbach’s alpha 0.85 to 0.94), a satisfactory singe-component factor structure (47% to 69% variability explanation power), and a good correlation (Pearson’s correlation 0.81 to 0.91) with the clinician-rated version [24]. The psychometric properties of the Internet-administered version of MADRS-S has found to be sufficiently similar to the pen and paper version [25,26].

Prospective participants meeting initial inclusion criteria will be interviewed via telephone according to the Mini-International Neuropsychiatric Interview (MINI) [27] manual. Diagnostic interviews conducted per telephone have previously been found to be in very good agreement with face-to-face interviews regarding major depressive disorder [28]. The screening interviews will be conducted by supervised, clinical psychology master’s students, trained in the use of MINI. The interviewers will meet together with experienced clinical psychologists and psychiatrists to discuss final inclusion and to tailor the respective treatment program to each participant. Randomisation of participants to the different groups will be done by a statistician not otherwise involved in the study, using a computer-generated list with variables not known to the principle researchers. Participants who drop out will not be replaced.

Participants will access treatment programs, register data and communicate with their therapists using an SSL-encrypted online interface. Participants will log in using their anonymous participant number, a chosen password and unique, single-use codes sent by SMS or ordinary mail.

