### Analysis

The study design will allow for multiple comparisons: the two physical exercise groups (separately and together) will be compared to controls, as will the two BA groups (separately and together). In all other analyses, the groups in question will include those from the control group later randomised to interventions, this to increase the statistical power. The two physical exercise groups will be contrasted with the two BA groups. Further, the physical exercise group with treatment rationale (group 1) will be contrasted with the group without (group 2), and the BA group with treatment rationale (group 3) will be contrasted with the BA group without (group 4). Finally, the four groups receiving relapse prevention will be contrasted with the four groups that do not. At the 12- and 24-month follow-ups, within-group comparisons will be made with previous results.

A number of statistical analyses will be deployed. Treatment outcomes will be examined using mixed effect models, Bonferroni-correcting for multiple comparisons. This method is deemed preferable to uni- and multivariate repeated measures of variance [40], especially since the study has built-in data-loss. The Kaplan-Meier estimator will be used to estimate survival rates during the study period. To find potential predictors of treatment outcomes (including treatment adherence and drop-out), logistic regression analysis on background variables will be performed (see [41]).

Since all questionnaire data will be supplied directly by the participants through the online interface, there is no risk of data loss or data distortion along the way. Data will be stored encrypted and in unidentifiable form (using participant-numbers). Standard missing data analysis will determine if unexpected missing data due to participant drop-out are random or not.

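### Secondary self-report outcomes have no in-treatment measurement, so their week-12 contrasts are unprotected against drop-out driven by in-treatment course; the weekly PHQ-9 offers a cheap partial remedy

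*Protocol article*

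**What the plan says.** The Screening and participants section lists the online screening battery, "consisting of MADRS-S, PHQ-9 [20], IPAQ [21], QOLI [22], GAD-7 [23", so these instruments have a pre-randomisation value. Secondary outcomes then gives the later schedule:

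- GAD-7: "GAD-7 will be administered upon treatment completion and thereafter monthly during the follow-up period".
- IPAQ: "IPAQ will be administered upon treatment completion and thereafter at the 12- and 24-month follow-ups".
- QOLI: "QOLI will be administered upon treatment completion and thereafter at the 12- and 24-month follow-ups".
- EQ-5D, with TiC-P on the same schedule: "At screening, as well as immediate after treatment and at the 12- and 24-month follow-ups, participants will also answer the EQ-5D".

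The primary outcome differs: "Participants will complete the PHQ-9 weekly during the treatment period, immediately upon completion of treatment and then monthly during follow-up (24 months". The abstract says that measurements "will be collected pre-treatment, weekly during treatment period, immediately post treatment and then monthly during a 24-month follow-up period" but names no instrument, so it does not extend the weekly schedule to the secondary questionnaires.

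The Control group section has the waiting list complete weekly measurements and then randomises it to treatment after 12 weeks. The Analysis section examines treatment outcomes with mixed effect models, and says that a standard missing data analysis will show whether drop-out is random.

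**The concern.** Every waiting-list comparison on anxiety, activity, quality of life, health status and costs rests on one post-randomisation measurement. At no later wave is the waiting list still untreated; the Discussion concedes that follow-up has no control group. A participant who stops answering for good at week 4 leaves up to four weekly PHQ-9 scores but only a screening value on the other instruments.

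A separate mixed model for such an outcome can condition on screening but not on how the person fared in treatment. In an Internet programme, people who are not improving are a plausible source of drop-out. The Ethics section also lets supervising clinicians end participation early when health appears to decline because of the intervention. That exit depends on course and cannot apply equally to the waiting list. The arm that loses more of its poor responders would look better than it is.

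**Working it through.** **1. Schedule, side by side**

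| Instrument | Screening | Weeks 1-11 | End of 12 weeks | Later |
|---|---|---|---|---|
| PHQ-9 | yes | weekly | yes | monthly to month 24 |
| GAD-7 | yes | none stated | yes | monthly to month 24 |
| IPAQ, QOLI | yes | none stated | yes | months 12 and 24 |
| EQ-5D, TiC-P | yes | none stated | yes | months 12 and 24 |

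The plan states no drop-out rate and no figure for the secondary outcomes, so there is no figure of its own to reproduce. Everything below rests on assumed inputs.

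**2. What a two-wave mixed model handles**

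With baseline modelled as an outcome, the estimated week-12 mean in an arm is: responders' week-12 mean + b × (baseline mean of all − baseline mean of responders). Baseline-only participants enter through the last term.

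Simulation: 100 per arm, baseline-to-week-12 correlation 0.5, true effect −0.50 SD, roughly 25% drop-out, 4,000 runs.

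| Drop-out depends on | Raw post-score, responders | Change score, responders | Baseline-adjusted, responders | Mixed model |
|---|---|---|---|---|
| nothing | −0.50 | −0.50 | −0.50 | −0.50 |
| baseline, differently by arm | −0.69 | −0.31 | −0.50 | −0.50 |
| unmeasured course, one arm only | −0.72 | −0.72 | −0.72 | −0.72 |

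The mixed model agrees with a baseline-adjusted analysis of responders, and it fails only in the third row. That row is severe (0.72 − 0.50 = 0.22 SD), because drop-out there depends on the very part of the week-12 score that baseline cannot predict, with log-odds rising 1.2 per SD.

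**3. Size when drop-out follows in-treatment PHQ-9**

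Assumed, in SD units and with no true difference:
- correlation of week-12 GAD-7 with screening GAD-7: 0.5
- correlation of week-12 GAD-7 with in-treatment PHQ-9: 0.65
- correlation of screening GAD-7 with in-treatment PHQ-9: r = 0.4, varied from 0.3 to 0.5
- drop-out log-odds rising by 1 per SD of in-treatment PHQ-9

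If p is the drop-out probability and p̄ its mean, responders' mean in-treatment PHQ-9 is too low by m = E[p(1−p)] / (1 − p̄). Integrating numerically over a standard normal:
- 15% drop-out: m = 0.113/0.85 = 0.133
- 25%: m = 0.160/0.75 = 0.213
- 35%: m = 0.190/0.65 = 0.292

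After adjustment for screening, the shift in week-12 GAD-7 is close to (0.65 − 0.5r) × m. The factor is 0.45 at r = 0.4, 0.50 at r = 0.3 and 0.40 at r = 0.5.

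| Scenario | Formula, r = 0.4 | r from 0.5 to 0.3 | Monte Carlo | Monte Carlo, PHQ-9 used |
|---|---|---|---|---|
| 25% in both arms, course-related in one | 0.45 × 0.213 = 0.096 | 0.085 to 0.107 | 0.097 | 0.000 |
| 35% v 15%, course-related in the 35% arm only | 0.45 × 0.292 = 0.132 | 0.117 to 0.146 | 0.131 | −0.002 |
| 35% v 15%, course-related in both | 0.45 × (0.292 − 0.133) = 0.072 | 0.064 to 0.080 | 0.074 | 0.000 |
| same rate and mechanism in both | 0 | 0 | −0.001 | 0.000 |

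The Monte Carlo columns use 1,500 trials per scenario and 125 per arm. The bias does not depend on arm size, so it carries over to the 100 per arm of the waiting-list contrast. The empirical SD of the estimate is about 0.13 with or without PHQ-9, so using PHQ-9 costs no precision.

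**4. How far the remedy reaches**

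The near-zero last column is partly built in, because drop-out was generated from the same PHQ-9 variable used to correct for it. Under other mechanisms, weekly PHQ-9 or an in-treatment GAD-7 removed about half to all of the bias. When drop-out depended on the unseen week-12 score, the figure was about 30%.

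**The case against.** Much of the opposing case stands.

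- **A reader might infer that the mixed model becomes a completers' analysis.** The document does not support this. It restricts no analysis to completers, and step 2 shows that drop-out depending on baseline and arm is handled.
- **A reader might infer that the authors rely on mixed models to protect these outcomes against drop-out**, from "This method is deemed preferable to uni- and multivariate repeated measures of variance [40], especially since the study has built-in data-loss". The loss meant there is the planned rotation of telephone interviews described under Diagnosis, which is missing completely at random by design. Drop-out is treated separately.
- **A reader might infer that the post-treatment questionnaires go only to those who finish the modules.** Design, Physical exercise, Behavioural activation and Relapse prevention together fix a 12-week period with measurements immediately after it, and nothing says that people who stop treatment are no longer asked. No rewording is needed.
- **Missing week 12 is not permanent loss.** GAD-7 returns monthly and the other instruments at 12 and 24 months. This helps comparisons among the four treatment arms when people resume answering. It gives no later untreated comparison with the waiting list, and nothing for those who never return.
- **Use of PHQ-9 as auxiliary information may already be in an analysis plan that is not shown.** That is fair, so its absence here is not an error. The questionnaire schedule, however, is fixed in this article, and an analysis plan cannot add measurements.
- **The biases are assumed and modest.** The largest in step 3 is about one empirical SD of the estimate and needs course-related drop-out in one arm only.
- **Pre/post measurement of secondary questionnaires is a legitimate burden trade-off.** Extra GAD-7 waves also do nothing directly for IPAQ, QOLI, EQ-5D or TiC-P.

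**Conclusion.** The point holds as an inexpensive improvement confined to the secondary outcomes. The plan does not contradict itself here. For GAD-7, IPAQ, QOLI, EQ-5D and TiC-P, the waiting-list contrast has one post-randomisation measurement and, analysed outcome by outcome, has no protection against drop-out driven by in-treatment course that differs between arms.

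Under the assumed correlations and drop-out of 15% to 35%, the bias is about 0.07 to 0.14 SD in favour of the arm that loses more of its poor responders. It is nil when rate and mechanism are equal. It could reach about 0.22 SD if drop-out tracks the unseen outcome itself, and the remedy is then weakest. None of these inputs comes from the protocol. The primary PHQ-9 analysis and the sample size of 500 are unaffected.

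**What to change.** 1. Analyse GAD-7, IPAQ, QOLI, EQ-5D and TiC-P with the weekly PHQ-9 scores as auxiliary information, either in a joint mixed model or by multiple imputation within arm that includes them. PHQ-9 should enter as an additional outcome or imputation variable. It is measured after randomisation, so using it as a covariate in the treatment-effect model would adjust away part of the effect.
2. Add the seven GAD-7 items to the existing weekly log-in at two in-treatment weeks (for example weeks 4 and 8), on the same calendar in all arms including the waiting list. The Control group section does not name the instrument in its weekly measurements; item 1 assumes that it is PHQ-9, and the protocol should say so.

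Cost: 2 × 7 = 14 extra items per participant and a slightly longer analysis, with no added staff, visits or participants. The bias reduction would be partial in practice, because drop-out may also depend on factors that no questionnaire captures.

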### Analysis

The study design will allow for multiple comparisons: the two physical exercise groups (separately and together) will be compared to controls, as will the two BA groups (separately and together). In all other analyses, the groups in question will include those from the control group later randomised to interventions, this to increase the statistical power. The two physical exercise groups will be contrasted with the two BA groups. Further, the physical exercise group with treatment rationale (group 1) will be contrasted with the group without (group 2), and the BA group with treatment rationale (group 3) will be contrasted with the BA group without (group 4). Finally, the four groups receiving relapse prevention will be contrasted with the four groups that do not. At the 12- and 24-month follow-ups, within-group comparisons will be made with previous results.

A number of statistical analyses will be deployed. Treatment outcomes will be examined using mixed effect models, Bonferroni-correcting for multiple comparisons. This method is deemed preferable to uni- and multivariate repeated measures of variance [40], especially since the study has built-in data-loss. The Kaplan-Meier estimator will be used to estimate survival rates during the study period. To find potential predictors of treatment outcomes (including treatment adherence and drop-out), logistic regression analysis on background variables will be performed (see [41]).

Since all questionnaire data will be supplied directly by the participants through the online interface, there is no risk of data loss or data distortion along the way. Data will be stored encrypted and in unidentifiable form (using participant-numbers). Standard missing data analysis will determine if unexpected missing data due to participant drop-out are random or not.

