## Methods/Design

### Design

This randomised controlled trial has been registered in clinicaltrials.gov (NCT01619930). It will feature four treatment groups and a waiting list control group with delayed treatment: (1) physical exercise without treatment rationale; (2) physical exercise with treatment rationale; (3) BA with treatment rationale; (4) BA without treatment rationale; and (5) a waiting list control group, the participants of which will be randomised evenly to the four treatment groups after a 12-week delay. Participants will be recruited in several cycles over an estimated period of 1 year, with the participants of every cycle being evenly distributed to the five groups. Even distribution of participants to the different cycles will be pursued. After the treatment period of 12 weeks, 50% of each of the four treatment groups will receive a relapse prevention program. All participants will be monitored for 24 months post treatment (Figure 1).

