The study aims to detect a moderate difference in the primary outcome measure (see section 2.4.3 below) with 80% power and a 5% significance level (Bonferroni-adjusted). In accordance with this, the study will feature 500 participants, with 100 in each treatment group (125 after the control group is dissolved and divided) and a total of 250 (half of each of the four treatment groups) receiving relapse prevention.

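### Plain Bonferroni over ten overlapping PHQ-9 contrasts is valid but gives up power that Holm's procedure would recover at the same 5% family-wise level

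*Protocol article*

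**What the plan says.** The Analysis section of the protocol article says of the control comparisons that "the two physical exercise groups (separately and together) will be compared to controls, as will the two BA groups (separately and together". That makes six contrasts. It then adds exercise against BA, exercise with against without rationale, BA with against without rationale, and relapse prevention against none, which brings the total to ten. The list carries no ranking. Within-group comparisons at 12 and 24 months are also mentioned, without a count.

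The multiplicity rule is a single sentence: "Treatment outcomes will be examined using mixed effect models, Bonferroni-correcting for multiple comparisons". The sample-size paragraph under Screening and participants builds on it: "The study aims to detect a moderate difference in the primary outcome measure" with "80% power and a 5% significance level (Bonferroni-adjusted", and "the study will feature 500 participants, with 100 in each treatment group" ("125 after the control group is dissolved and divided"). It gives no divisor, numerical effect size or standard deviation.

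The schedule of the primary outcome is: "Participants will complete the PHQ-9 weekly during the treatment period, immediately upon completion of treatment and then monthly during follow-up (24 months".

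**The concern.** Single-step Bonferroni compares every p-value with the same reduced level, however many of the other contrasts have already been rejected. It also ignores overlap, and this list overlaps heavily: each pooled control contrast is the average of the two single-arm contrasts beside it, and all six control contrasts share the same 100 controls. Another procedure is at least as powerful in every data set, needs no further assumption and holds the same family-wise rate. At stake is some power on each question the trial asks, in a trial whose size was set after the Bonferroni adjustment.

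**Working it through.** **Inputs.** Overall alpha 5% and power 80% (sample-size paragraph); 100 per group including controls ("the study will feature 500 participants, with 100 in each treatment group"; "with the participants of every cycle being evenly distributed to the five groups"); 125 per treatment group once the controls cross over, hence 250 v 250 for exercise against BA and for relapse prevention. Assumed because not stated: two-sided tests, SD = 1, d = 0.5 for a moderate difference (d = 0.4 also shown), no drop-out.

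**Count of contrasts.** 3 + 3 + 1 + 1 + 1 + 1 = 10, so the flat Bonferroni level is 0.05/10 = 0.005. Ten is the natural reading of the list, not a stated divisor.

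**The plan's own figure.** With n per arm = 2(z₁₋α/₂ + z₀.₈₀)²/d² and alpha = 0.05/m:
- m = 6 gives 97, m = 7 gives 100, m = 8 gives 103.
- m = 10: 2(2.807 + 0.842)²/0.25 = 106.5, so 107.

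At d = 0.5 the stated 100 per group fits six to eight comparisons better than ten. With neither d nor m stated, this cannot be settled.

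**Power under flat Bonferroni (0.005, critical value 2.807).**
- One arm v control, 100 v 100: SE = √(2/100) = 0.1414; 0.5/0.1414 = 3.536; Φ(3.536 − 2.807) = 76.7%.
- Two arms pooled v control, 200 v 100: SE = √(1/200 + 1/100) = 0.1225; 0.5/0.1225 = 4.082; Φ(4.082 − 2.807) = 89.9%.
- Relapse prevention, 250 v 250, d = 0.3: SE = √(2/250) = 0.0894; 0.3/0.0894 = 3.354; Φ(3.354 − 2.807) = 70.8%.

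**Why Bonferroni is conservative here.** Two single-arm contrasts share the control mean, so their correlation is (1/100)/(2/100) = 0.5. A single-arm contrast and the pooled contrast containing it have covariance 1/100 + ½ × 1/100 = 0.015, so their correlation is 0.015/√(0.02 × 0.015) = 0.87. Simulating the ten correlated test statistics with every null true, at least one falls below 0.005 in 3.8% of trials. A single-step level of about 0.0067 would use the full 5%.

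**Holm.** Order the ten p-values. Compare the smallest with 0.05/10, the next with 0.05/9, and so on up to 0.05/1, stopping at the first failure. Every threshold is at least 0.005, so whatever Bonferroni rejects, Holm rejects too. The 5% family-wise rate holds under any dependence, as it does for Bonferroni. Simulated power (at least 200,000 draws per setting):

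| Contrast | Bonferroni | Holm |
|---|---|---|
| One arm v control, d = 0.5 | 77% | 81-83% |
| Pooled arms v control, d = 0.5 | 90% | 91-92% |
| Relapse prevention, d = 0.3, all arms d = 0.5 v control | 71% | 79% |
| One arm v control, d = 0.4 | 51% | 56% |
| Pooled arms v control, d = 0.4 | 68% | 70% |

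At d = 0.5, the lower Holm figure takes the four non-control contrasts as null and the upper one adds a relapse-prevention effect of d = 0.3. The d = 0.4 rows take the non-control contrasts as null. With all ten nulls true, Holm's error is the same 3.8%, because its first step is the Bonferroni step. Its gain comes once some contrast is rejected.

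**Drop-out.** With an assumed 20% loss, the flat Bonferroni figures at d = 0.5 fall to 63.9% (one arm) and 80.1% (pooled).

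**The case against.** The best defence is that Bonferroni is valid, simple and already allowed for in the sample size, and that the loss is modest: one to two points for a pooled contrast and four to six for a single arm. All of that stands, so this is an improvement and not the repair of an invalid analysis.

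Three stronger readings are tempting, and the documents do not support them.

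- *Inflated type I error.* A reader might infer that the many PHQ-9 assessments and secondary outcomes escape the correction. The article does not say that the adjusted level is reused at each visit or for each outcome, and a mixed model on repeated PHQ-9 scores need not give one test per visit. Testing exercise against control three ways inflates nothing either: at 0.005 each, the chance that any of the three is falsely positive is 1.1%.
- *Contradictory conclusions on one treatment.* At d = 0.5 the pooled exercise test is significant while at least one arm is not in 26% of trials. That is mostly one arm missing significance at 100 v 100. The pooled test is significant with neither arm significant in only about 3%. The separate arms also serve a stated aim, the effect of giving a rationale, so they are not mere repetition.
- *No deciding contrast, time point or divisor.* A statistical analysis plan commonly supplies these, and it is not shown. The waiting list also ends after 12 weeks, which already confines the control comparisons to that period.

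**Conclusion.** The concern holds as a point of efficiency. The article commits itself to single-step Bonferroni over a list of ten overlapping contrasts, and Holm is never worse at the same 5% family-wise level. At d = 0.5 without drop-out, the gain is about 4-6 percentage points for a single arm against control and 1-2 for a pooled contrast. It is about 8 points for relapse prevention at d = 0.3. These sizes rest on normal outcomes, two-sided tests, d = 0.5 as the meaning of moderate, and ten as the family. If the intended family is smaller, the amounts change, but it remains true that Holm never rejects less.

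**What to change.** In the Analysis section, replace Bonferroni with Holm correction over the ten listed PHQ-9 contrasts, each at one named time point. For the six control contrasts that is the end of the 12-week treatment or waiting period; the investigators should name it for the other four. In writing out the list, the exercise labels need reconciling: the Design section defines group 1 as without rationale, and the Analysis section calls it the group with rationale.

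The cost is a change of wording before data are seen. The only statistical downside is that simultaneous confidence intervals matching Holm are less direct than Bonferroni intervals.

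Whether to rank some contrasts as primary is the investigators' choice. A hierarchy that tests the remaining contrasts only after both pooled waiting-list contrasts succeed is not recommended. It would put exercise against BA, the comparison with which the Abstract opens, behind both. If exercise were d = 0.2 and BA d = 0.5, that gate would cut power from 71% under flat Bonferroni to 27% for exercise against BA, and from 71% to 31% for relapse prevention at d = 0.3.
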